### Qualitative analysis of the interviews and focus groups

Qualitative content analysis [39, 40, 48, 49] will be used to evaluate the interviews and focus groups. The evaluations will be carried out with the programme MAXQDA 12. To systematically describe content-relevant topics using a category system, all transcripts will be reviewed to identify interesting content-related aspects. The main topics (main categories) will be derived deductively from the research questions and interview guidelines, and subcategories will be developed inductively from the material, for example, by subsumption [40]. To test the category system, two scientists will independently test-code part of the material, followed by a modification of the categories and their definitions. The entire coding process will be performed using consensual coding [49], i.e., the transcripts will initially be coded independently by two scientists. Afterwards, the codings will be brought together, and a consensus will be reached.

### Analysis of the cockpit data

In the cockpit, the relevant user statistics will be continuously updated and visualized. The final features of the cockpit visualizations will be defined during the user-centred design process, but certain functions are canonical. Envisaged are, among other features, graphical displays showing frequencies, duration and cessations of video sequences. This information can be inspected individually for a particular patient or comparatively across all patients.

## Discussion

Regular physical activity has high curative potential for chronic and degenerative diseases [50]. Against the background of demographic change, a higher number of chronically ill and elderly people are expected to need support for carrying out physical activity. In addition, the care of PD patients in an outpatient setting is deficient (especially in rural areas). Through this proposed tablet-based programme, patient competence and compliance can be increased and the general aftercare improved. Additionally, the app can easily be customized and extended to meet other indications. It could thus be made available to all people who need help with home-based training.

### Innovation factor

For the first time, our tablet-based training programme ensures continuous and long-term support for PD patients. Physically activating exercises and physical activities are initiated at the beginning of the MKP and continued at home. PD patients learn various self-management strategies during and after their MKP and are empowered to assume responsibility for carrying out regular physical activity on their own. Through the tablet-based training programme, all PD patients receive high-quality care in the implementation of physically activating exercises and physical activity, regardless of their place of residence. Finally, our project also closes a gap at the level of available applications. In the most common app stores, there is no scientifically evaluated app in German that is integrated into the overall treatment of the patient and could support the patients in self-managing their disease. In addition, the user-centred development of the app ensures that the app meets the specific needs of PD patients.

### Immediate expected results of the project

Through the personalized training programme, we expect an increase in physical activity that positively affects the motor and non-motor impairments of PD patients and thus improves quality of life. Due to the regular supervision and adaptation of the training programme, we assume that the positive effects of MKP can be maintained longer and that a slowing down of the course of the disease can be achieved. Due to the high proportion of self-performed physically activating exercises and physical activity in our intervention, individualized, time-consuming care by a therapist can be significantly reduced. It can be assumed that costs can significantly be saved in comparison to conventional occupational and/or physiotherapy prescriptions. The physical and everyday obstacles that PD patients face in executing and maintaining physical activity are considered in our individual training plan and in the preparatory and accompanying measures (such as patient-centred seminars and telephone and in-person support). Thus, the intervention meets the specific needs and requirements of this particular patient clientele and should therefore achieve high acceptance and adherence.

### Transferability of the project results to the everyday care situation

The intervention to be examined in this study will be established and evaluated as an example in a specialty clinic for the treatment of PD. In principle, however, this intervention can also be transferred to other clinics. Patients’ desires for long-term and continuous care are met in this intervention. The exact time and personnel resources required for the implementation of the intervention (for telephone calls, onsite appointments) will be measured in the context of this project and are therefore available as key data for the establishment of the programme in other clinics.

The app to be developed in this project can be integrated into other telemedicine developments for Parkinson’s treatment [51]. The basic structure of server-side cockpit functionality, data transfer through the app, and graphical user interfaces is implemented modularly. The frontend for the selection of videos can therefore be easily replaced or supplemented by alternative modules with a different content focus.

## Limitations

A disease-specific (but rather small) risk is that the disease might deteriorate significantly. In this case, an exercise adjustment will be made in the “negative direction” to ensure that the patient does not feel overwhelmed and can continue training despite deterioration. From a technical point of view, there are risks concerning the possible failure of tablets and the possible breakdown of the data connection in the mobile radio channels. For data transmission, an intelligent mechanism is implemented that repeats transmission attempts in cases of failure after variable time intervals. Because the data are not time-critical, this problem is negligible. In the event of malfunctioning terminal devices, a pool of replacement devices and a strategy for easily transferring the patient-specific settings to the replacement device are maintained. Data security is planned on two stages. In addition to the use of conventional encryption techniques on the data lines, specific encodings of the semantic meaning of the user statistics will be developed that cannot be interpreted by outsiders. Personal data will never be transmitted via a data line. Another risk could arise if changes occur in the structural characteristics of the treated patients after recruitment of the CG is completed. To detect this risk, patient characteristics will be collected and compared for both groups. Existing differences will be adequately included in the analyses (e.g., as covariates in multivariate methods or by propensity score matching). Based on our current knowledge, we assume that the occurrence of such relevant structural changes in the context of the project is unlikely.

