## Methods

### Eligibility criteria

All patients admitted to our partner clinic for a three-week MKP with a diagnosis of idiopathic Parkinson’s syndrome will be eligible to participate (ICD G20.0 and G20.1). Concomitant care and interventions as e.g. privately organized physiotherapy sessions after the MKP are allowed.

Exclusion criteria: Montreal Cognitive Assessment (MoCA) < 18 points, Berg Balance Scale < 41 points, a major depressive episode, moderate to severe dementia, and cardiovascular and orthopaedic/surgical reasons that argue against independent home training. Participants will be also excluded from the study if they are being admitted to an acute hospital during their MKP.

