### Case number calculation / sample size

With regard to the changes in the primary outcome, we assume that both groups (the CG and IG) will have improved in a similar way at the end of the MKP. According to our assumptions, the effect of the CG during the subsequent period will approach the starting level again, while the positive changes in the IG will stabilize or even increase slightly. To estimate the required sample size, we have referred to the results of existing studies on the influence of physical activity on quality of life (PDQ-8) in PD patients. For the effect determination, the data of Ebersbach et al. [46], Morris et al. [47] and Nadeau et al. [10] are being consulted. In Ebersbach et al., the quality of life over a 4-month course showed effect sizes of average magnitude (ES = 0.47) for patients who underwent physical training (Nordic walking), whereas there was no change in the CG. Morris et al. also report a significantly improved quality of life, with a mean effect size of ES = 0.45, after muscle training over a 3-month span. In their controlled study on the effect of intensive treadmill training (speed and incline) on quality of life, Nadeau et al. found an effect size of ES = 0.73 over a 6-month course; for simple treadmill training, they found an effect strength of ES = 0.21. In the CG, the quality of life did not change. For the calculation of the number of cases, we assume that participation in the tablet-based training programme (IG) will lead to clinically relevant positive effects (t_0_ vs. t_2_ ES = 0.40) on quality of life (PDQ-8) 9 months after the end of MKP. In contrast to the IG, there will be no changes in the CG at t_2_. To demonstrate differences between the IG and CG 9 months after MKP on the order of at least ES = 0.4 with two-sided testing at α = 5% and a power of 80%, a group size of *N* = 100 net is required for each IG and CG. We expect only a moderate dropout rate of 25% among patients after MKP due to their attachment to the clinic. Thus, to be able to evaluate N = 100 patients per group, 133 participants per study group must initially be included. Approximately 120 PD patients participate in the MKP per quarter at the partner clinic. Based on the defined inclusion and exclusion criteria, we expect 70 patients per quarter to be included in the study. The recruiting of the CG and IG will take place over a period of nine months each. Taking into account a rate of study refusal of 25%, the targeted number of cases in the clinic can be recruited within this time frame.

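### Confounder adjustment in this sequential, non-randomised comparison depends on group differences seen in the data and leaves the method open; a short covariate set should be fixed in advance and always used

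*Protocol article*

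**What the plan says.** Under Study design, part A (quantitative measures), all patients of a first recruitment period form the control group and all patients of a second period form the intervention group. Nobody is blinded. The Quantitative analyses section plans repeated analysis of variance on complete cases and names no covariates; age, sex and education appear only as subgroup factors.

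The Limitations section recognises that the patient mix may change between the two periods. It says characteristics will be compared between the groups and then: "Existing differences will be adequately included in the analyses (e.g., as covariates in multivariate methods or by propensity score matching"). It gives no criterion for a difference and does not choose between the two methods. It adds that a relevant change is thought unlikely.

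The sample size section aims to show "differences between the IG and CG 9 months after MKP on the order of at least ES = 0.4". The test is two-sided at the 5% level with 80% power, and the section concludes that "a group size of *N* = 100 net is required for each IG and CG". The only allowance is for dropout: "We expect only a moderate dropout rate of 25% among patients after MKP", hence "Thus, to be able to evaluate N = 100 patients per group, 133 participants per study group must initially be included".

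Several prognostic variables will be at hand. Table 1 lists PDQ-8, comorbidity, physical activity and sociodemographic data at t0, and screening applies the limits "Montreal Cognitive Assessment (MoCA) < 18 points, Berg Balance Scale < 41 points".

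**The concern.** When groups are formed by calendar period, the bias from a measured factor is its imbalance multiplied by its prognostic strength. Whether the imbalance was noticed does not enter. A rule that adjusts only for differences seen will often leave moderate imbalances in place. It also postpones the choice of covariates and of method until the groups have been compared, in an unblinded study.

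The second issue is the option of matching. Matching discards patients without a counterpart, and the planned size has nothing in hand for that.

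This is not merely detail that an article leaves to a fuller document. The article itself states a data-dependent rule, and an analysis plan that followed it would inherit the weakness.

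**Working it through.** **1. The plan's own figure.** Inputs from the sample size section: ES 0.4 (SD = 1), two-sided α = 5%, power 80%. The formula n = 2(1.96 + 0.84)²/0.4² gives 98 to 99 per group depending on rounding of the quantiles (99 after rounding up); the t-based solution is 99.08, hence 100. Dropout: 100/0.75 = 133.3, stated as 133. Both figures reproduce.

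**2. How often an imbalance is missed.** The document gives no criterion, so a 5% two-sample t-test is assumed. With 100 per group, the power to detect a true imbalance of 0.2 SD is 29.1% and of 0.3 SD 56.0%. They are missed in about 71% and 44% of trials.

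**3. Bias left in a final-score comparison at t2.** Let D be the observed imbalance, with mean 0.2 and SE = √(2/100) = 0.141. The rule leaves the estimate unadjusted when |D| < 1.96 × 0.141 = 0.277. The mean of D over those trials, counting the others as zero, is approximately

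0.2 × Φ(0.546) − 0.141 × φ(0.546) = 0.2 × 0.707 − 0.141 × 0.344 = 0.093.

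Multiplied by the confounder-outcome correlation ρ, this is the mean bias under the rule:

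| ρ (assumed), imbalance 0.2 SD | Never adjusted (0.2 × ρ) | Adjusted if p < 0.05 (0.093 × ρ) | Always adjusted |
|---|---|---|---|
| 0.3 | 0.06 | 0.028 | 0 |
| 0.5 | 0.10 | 0.046 | 0 |
| 0.7 | 0.14 | 0.065 | 0 |

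Simulation (6,000 trials per scenario, no treatment effect) gives 0.029, 0.044 and 0.067 for the third column. The type I error under the rule was 5.3% to 5.8% at this imbalance and at most 6.9% at 0.3 SD.

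**4. Bias left in the planned group-by-time contrast.** For the change from t0 to t2, only the difference between the confounder's correlations with the two scores matters. Results are in SDs of the PDQ-8 score, imbalance 0.2 SD:

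| Correlation with t0 / t2 (assumed) | Never adjusted | Adjusted if p < 0.05 |
|---|---|---|
| 0.7 / 0.7 | 0.2 × 0 = 0 | 0 |
| 0.5 / 0.6 | 0.2 × 0.1 = 0.02 | 0.093 × 0.1 ≈ 0.01 |
| 0.3 / 0.5 | 0.2 × 0.2 = 0.04 | 0.093 × 0.2 ≈ 0.02 |

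A simulation on change scores agrees. Against the target of 0.4, 0.02 SD is 5%; the final-score upper value of 0.065 SD is about 16%.

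**5. If matching is chosen.** The evaluable number is 133 × 0.75 = 99.75 per group, so there is no reserve. The loss rates below are assumptions; power is for a two-sample t-test at ES 0.4.

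| Loss to matching | n per group | Power | Enrolment per group to keep 100 |
|---|---|---|---|
| 0% | 100 | 80.4% | 134 |
| 10% | 90 | 76.1% | 149 |
| 20% | 80 | 71.0% | 167 |

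The recruitment forecast is that "we expect 70 patients per quarter to be included in the study". Over three quarters and after 25% refusal this gives 70 × 3 × 0.75 = 157 per group, enough for a 15% loss (100/0.85/0.75 = 157) but not for 20%.

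**6. Fixed covariates instead.** All 100 per group are kept. If the covariates together correlate 0.3 or 0.5 with the outcome, the residual SD is √(1 − r²) and power becomes 84.3% or 90.4%, before any variance inflation from imbalance between the groups.

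**The case against.** The best defence is that the planned repeated analysis already uses t0 PDQ-8. A factor that relates equally to t0 and t2 cancels, and what the conditional rule then leaves is about 0.02 SD or less per factor under the assumptions tried. This stands, and it limits the point. A reader might infer that adjustment is the design's only protection against confounding, or that substantial bias will remain in the primary result. The documents support neither: there is a baseline measurement of the outcome, consecutive assignment at one clinic, common eligibility limits and a record of inpatient treatment to check equal care. The 0.14 and 0.065 SD values need a final-score analysis, a correlation of 0.7 and, for the latter, a 5% test; the document states none of these.

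A reader might also infer that the plan loses its 80% power. Matching is only one of two examples, and the loss arises only if it is chosen and leaves patients unmatched.

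Finally, an article may leave the exact covariate list to a fuller document. That is fair for the list. It does not cover the rule itself, which is stated here and is conditional on the observed data.

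Adjustment can also be overdone. Calendar season looks like a natural covariate, but each group is recruited over nine months, one after the other. If the periods are contiguous and recruitment even (assumptions), some months occur in one group only. Adjusting for season then inflates the variance of the group effect by about 1.09 to 1.5, and power at ES 0.4 falls to about 77% down to 63%, before any gain from other covariates.

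**Conclusion.** The point holds in a limited form and should be fixed. The plan makes adjustment for measured confounders conditional on differences seen in the data and leaves both covariates and method open, in a non-randomised comparison whose named analysis has no covariates. Moderate imbalances can stay unadjusted, and the model can be chosen after the data are seen.

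The likely bias per measured confounder is small in the planned change contrast and moderate at most in a final-score comparison. Several confounders acting in the same direction could add up. These sizes rest on an assumed 5% test, an imbalance of 0.2 SD and assumed correlations. The loss of power is conditional on matching and on assumed loss rates. The open choice of model after seeing the data does not depend on any of these assumptions.

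**What to change.** In the Statistical methods section, name a short set of baseline covariates that are already collected, for example t0 PDQ-8, age, sex, education, comorbidity, t0 physical activity, and the MoCA and Berg values from screening. Include them in the primary model whatever differences are observed.

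State how they enter. If t0 PDQ-8 stays as the first repeated measure, it cannot also be a covariate, and the other covariates must interact with time, since a covariate main effect alone leaves the group-by-time contrast of complete cases unchanged. Otherwise, use t0 PDQ-8 as a covariate for the later score.

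Remove propensity score matching as a primary option. Use propensity weighting on the same covariates as a sensitivity analysis that keeps all evaluable patients. Examine calendar season in a sensitivity analysis only.

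The cost is a few degrees of freedom out of about 200 patients, and transfer of the screening values to the study file under the pseudonymous ID. The sample size need not rise. Unmeasured differences between the two recruitment periods remain, whatever is adjusted, and should be acknowledged.

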## Data Availability

The datasets generated and/or analysed during the current study are not publicly available. Declaration of consent does not include release of the data for external analyses. A model consent form is available from the corresponding author by reasonable request. Trial results will be published and thus be made available to anyone interested in the study. It is not planned to make IPD available. The trial protocol, participant-level dataset, and statistical code for generating the results will also not be made publicly available.

## Abbreviations

MKP: Multimodale Komplexbehandlung bei Morbus Parkinson is a three-week inpatient programme for PD patients in which they receive drug therapy as well as units in physiotherapy, occupational, music, sports and speech therapy and neuropsychology.
OPS: Operationen- und Prozedurenschlüssel (the German Operations and Procedures Key) is used to encode operations and medical procedures in inpatient care as well as in outpatient surgery in the clinic.
PD: Parkinson’s disease
